### Outcome measures

The primary outcome measure for this study is the mean total ASQ-3 score, and the secondary outcomes are the following:

Proportion with one or more ASQ-3 domain scores below the established cut-offs which identify possible developmental delay.Proportion of ASQ-3 domain scores below the established cut-offs which identify possible developmental delay.Mean ASQ-SE-2 total score and proportion of ASQ-SE-2 total scores above the established cut-offs which identify possible developmental delay.Mean LRSQ total score.Frequency of healthcare usage.

### Sample size

The study sample size aims to be able to detect a difference in neurodevelopment associated with perinatal SARS-CoV-2 exposure of similar magnitude to that seen in term-born infants with mild neonatal encephalopathy: a difference in developmental score of 6 points (0.5 SD).^32^ Therefore, to detect a similarly clinically meaningful between-group difference of 0.5 SD in mean ASQ-3 total score (mean (SD) 203.02 (50.84))^33^ in exposed versus comparison infants, with a type-I error of 0.05 and 90% power, we will need a minimum of 85 infants in each of the two exposure groups and in the comparison group.

To achieve a sufficient sample size for future follow-up studies at school-age considering potential attrition, we aim to recruit at least 200 children in each group. Given the 20% response rate in a previous study of similar design using the UKOSS platform,^34^ we will approach the parents of up to 1000 children in the antenatal exposure cohort (currently there are around 830 eligible antenatal exposure cohort children) and up to 2000 families for the comparison cohort, as we expect response rates to be lower for the comparison cohort. Given that there are around 120 eligible children in the neonatal exposure cohort to date, we will approach the parents of all these infants. Consequently, our target sample size comprises 200 children in the antenatal exposure cohort, 200 in the comparison cohort and up to 120 children in the neonatal exposure cohort.

Patient and public involvement

The study design was discussed with a patient and public involvement (PPI) group consisting of a parent of an infant exposed to SARS-CoV-2 in the antenatal period and another parent whose infant was exposed to SARS-CoV-2 in the neonatal period. The PPI group agreed that the research question is important and the design and outcomes to be measured are appropriate. The parent information sheet and consent form were developed with input from the PPI group, and further PPI will be sought to support the conduct of the study and help with interpreting the results.

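### The neonatal cohort's target is only a ceiling: at the one response rate the plan cites it would yield about 24 infants, not the required 85, with about 64% power rather than 90%

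*Protocol article*

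**What the plan says.** All the relevant text is in the Sample size section of the protocol article. The target effect is a "clinically meaningful between-group difference of 0.5 SD in mean ASQ-3 total score", "with a type-I error of 0.05 and 90% power". From this the plan concludes that "we will need a minimum of 85 infants in each of the two exposure groups and in the comparison group".

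It then turns to recruitment. It opens with "Given the 20% response rate in a previous study of similar design using the UKOSS platform" and proposes to approach up to 1000 antenatal families for a target of 200. For the comparison cohort it expects a lower response and proposes up to 2000 families, also for 200.

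The neonatal cohort is treated differently: "Given that there are around 120 eligible children in the neonatal exposure cohort to date, we will approach the parents of all these infants". The target listed for it, next to 200 and 200, is "up to 120 children in the neonatal exposure cohort". The article gives no neonatal response rate, no expected number of participants and no power at that number. It does not say that the minimum of 85 might be missed.

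**The concern.** Two of the three cohorts are discounted for non-response and the third, which has by far the smallest pool, is not. The neonatal target equals the whole eligible pool, so it says nothing about how many infants will be analysed. The minimum of 85 was set for both exposure groups and is not revisited once the pool is known to be about 120.

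The primary objective covers antenatal and neonatal exposure, so the neonatal comparison is one of its two parts. The article says the results will inform advice to parents of exposed newborns. If few neonatal families respond, a non-significant difference could be read against the only power figure in print, 90% at 0.5 SD, and taken as evidence that an effect of that size is absent. The data might not support that reading.

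**Working it through.** **Inputs from the Sample size section.** Type I error 0.05; power 90%; difference 0.5 SD; SD of the ASQ-3 total 50.84, so the difference is 0.5 × 50.84 = 25.4 points; minimum 85 per group; response rate 20%; about 120 eligible neonatal children, all to be approached; comparison target 200. The plan does not state sidedness.

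**Step 1: reproduce the plan's figure.** n per group = 2(1.960 + 1.282)² / 0.5² = 84.1, rounded up to 85. This matches. A one-sided test would give 69, and a two-sided level of 0.025 would give 100. The plan therefore used a two-sided 5% test with equal groups.

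**Step 2: neonatal yield at the cited rate.** 120 × 0.20 = 24 infants, which is 24/85 = 28% of the stated minimum. Response needed for 85: 85/120 = 71%. Eligible children needed for 85 at 20%: 85/0.20 = 425, about 3.5 times the stated pool.

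**Step 3: power against the planned 200 comparators.** Normal approximation: power = Φ(0.5 / √(1/n + 1/200) − 1.960). For n = 24, √(1/24 + 1/200) = 0.2160 and 0.5/0.2160 = 2.315, so power = Φ(0.355) = 63.9%. The t-test version gives 63.5%.

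**Step 4: difference detectable with 90% power.** This is 3.2415 × √(1/n + 1/200) SD. For n = 24 it is 3.2415 × 0.2160 = 0.70 SD, and 0.70 × 50.84 = 35.6 points.

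Only the 20% rate below appears in the plan. The other rates are assumptions, shown to give the range.

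| Response | Neonatal n | Power at 0.5 SD, normal (t-test) | Detectable with 90% power |
|---|---|---|---|
| 20% | 24 | 63.9% (63.5%) | 0.70 SD, 35.6 points |
| 30% | 36 | 78.9% (78.5%) | 0.59 SD, 29.8 points |
| 40% | 48 | 87.5% (87.3%) | 0.52 SD, 26.5 points |
| 50% | 60 | 92.5% (92.3%) | 0.48 SD, 24.3 points |

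**Step 5: smallest neonatal group that gives 90% power with 200 comparators.** The answer is 54 infants (t-test power 90.1%), and 54/120 = 45% response. This is fewer than 85 because the comparison group is larger than the equal-group calculation assumes.

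**Step 6: what a null result could exclude.** With 24 against 200, the unadjusted 95% CI has a half-width of about 1.960 × 0.2160 = 0.42 SD. It would exclude a 0.5 SD deficit only if the observed deficit were below about 0.50 − 0.42 = 0.08 SD.

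**The case against.** The strongest reply is that 20% is not a neonatal rate. It comes from a study on the UKOSS platform, whereas the neonatal cohort is identified through the BPSU study. The plan itself treats response as differing between cohorts. Hospitals receive the NHS number and date of birth for neonatal cases, may telephone before posting, and non-responders are sent a reminder pack. Parents of a hospitalised infected newborn may also respond more readily. All of this stands: the neonatal rate is unknown, and 24 is a yield at an assumed rate, not a forecast.

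A reader might infer that the cohort cannot reach 90% power. The documents do not support that. With 200 comparators, 45% response is enough, and nothing in the article rules that out. A reader might also infer that the plan assumes every family will take part. It does not, because the wording sets an upper limit on a small pool. The fair criticism is narrower: a ceiling is listed as the target without an expected yield beside it.

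It can also be said that 85 is stated as a need, that no sentence promises the neonatal cohort will meet it, and that a fuller protocol may give power by cohort. The first two are correct as a reading of the text. Even so, the article prints the minimum, the rate, the pool and the target in one section, and at the printed rate they do not fit together. That is a fault in what is stated, not a detail left to another document.

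Finally, the pool is described as the count to date and might grow. Births are limited to 1 March 2020 to 28 February 2021 and infection to the first 28 days, so late ascertainment could add some children. Growth to 425 is not plausible on these terms.

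**Conclusion.** The point holds in conditional form. At the only response rate the plan cites, the neonatal cohort would supply about 24 infants instead of 85. Power at 0.5 SD would be about 64% against 200 comparators, and the difference detectable with 90% power about 0.70 SD. Over assumed response rates of 20% to 50%, power runs from about 64% to 92% and crosses 90% at about 54 infants.

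These figures assume a two-sided 5% test, an unadjusted two-group comparison, the plan's SD of 50.84, 120 families approached and the full 200 comparators recruited. The calculation of 85 is correct. The fault is that it is not carried through to the neonatal cohort.

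The antenatal cohort is not affected. A reader might add that the roughly 830 antenatal children eligible so far would give 830 × 0.20 = 166, below 200. But the 200 is set for later school-age follow-up, up to 1000 families may be approached, and 166 against 200 still gives more than 99% power at 0.5 SD.

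**What to change.** In the Sample size section:

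- Replace the ceiling as the neonatal target with an expected yield over a range of response rates labelled as assumptions, for example 24 to 60 infants for 20% to 50%.
- Give the neonatal power at 0.5 SD and the difference detectable with 90% power at those yields, against 200 comparators.
- Limit the 90% power statement to the antenatal comparison unless at least about 54 neonatal infants are obtained.
- State that the neonatal result will be interpreted from its estimate and 95% CI, so that a null result is not read as excluding 0.5 SD.

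The cost is a change of wording, and the stated neonatal power becomes less favourable. No extra recruitment is needed, since every known eligible neonatal family is already to be approached.

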### Data analysis

We will use descriptive characteristics to compare the exposed and comparison cohorts and assess their representativeness (against national surveillance data, and data from the Office for National Statistics and National Records for Scotland, for the exposed and comparison cohorts, respectively). We will use multiple linear and logistic regression to compare primary and secondary outcomes between the exposed and comparison cohorts, adjusting for potential confounders (eg, baseline sociodemographic factors including ethnicity, sex, socioeconomic status) and carry out exploratory subgroup analyses by gestation for antenatal exposure and severity of SARS-CoV-2 infection in the neonatal period. We will also conduct sensitivity analysis to evaluate the impact of children with other conditions that could impact neurodevelopment including hypoxic-ischaemic encephalopathy, seizures, perinatal stroke, bacterial or non-SARS-CoV-2 viral meningitis and neuroimaging abnormalities in the neonatal period.

## Discussion

The neuroinvasive potential of SARS-CoV-2 was speculated on formulating the study protocol, as some adults with moderate/severe SARS-CoV-2 infection presented with neurological manifestations,^35^ raised neuronal injury and glial activation markers,^36^ and as the ACE-2 receptor for SARS-CoV-2 is expressed on neurons, glial cells and oligodendrocytes.^37–39^ This speculation has since been supported by evidence linking SARS-CoV-2 infection to brain abnormalities and cognitive deficits in adults.^17 18 20 21^

Currently, there is a lack of representative studies examining the impact of maternal SARS-CoV-2 infection in pregnancy and neonatal SARS-CoV-2 infection on the long-term neurodevelopment outcomes of infants. Identifying whether children in these cohorts may be at increased risk of developmental delay is important, as this will inform public health advice provided by the NHS and clinicians to pregnant women and parents of newborn children exposed to SARS-CoV-2 infection.

### Ethics and dissemination

Approval was obtained from London-Westminster Research Ethics Committee (REC; protocol no: 2021-93), and subsequent amendments to the protocol requiring REC approval were implemented after revised documents were reviewed and approved by the REC and participating organisations. Non-substantial amendments including the addition of new sites were reviewed by the sponsor, submitted to the Health Research Authority (HRA) for information only, and shared with the participating organisations. Findings will be disseminated in scientific conference presentations and peer-reviewed publications.

## Data Availability

No data are available.
